##### Health state

The health state will be evaluated by the mean change of SF-36 [22] from baseline, which is a questionnaire consisting of 36 items, including two subscales (physical subscale and psychological subscale). The scores on each subscale range from 0 to 100. Lower scores indicate a worse health state.

#### Laboratory tests

Laboratory tests will be performed at two time points: baseline and at the end of treatment. In the morning, after the participant has fasted for at least 12 h, venous blood and urine will be collected at the First Affiliated Hospital of Changchun University of Chinese Medicine. Metabolomics tests will be conducted at The Jilin Ginseng Academy of Changchun University of Chinese Medicine.

Ultraweak photon emission (UPE) [23, 24] will be carried out with the biological ultraweak photon emission signal acquisition system (PMS09.1) at the Acupuncture and Moxibustion Research Institute of Changchun University of Chinese Medicine. These measurements will be performed at the baseline and at the end of the treatment time points. During the testing period, participants will wear black clothes and enter a darkroom. UPE will be detected at the RN12 acupoint before 12 a.m. over a 20-min period. The purpose of this test is to detect mean changes in UPE before and after acupuncture and to explore the mechanisms of acupuncture treatment on FD based on energy metabolism.

#### Adverse events

Any adverse events reported by the participants will be recorded in the case report form (CRF), including the time, symptoms, signs, degree, duration, laboratory test index, treatment and outcome, follow-up, and follow-up time. Common treatment-related adverse events include subcutaneous hematoma, continuous post-needling pain, itching at the sites of the needle insertion, and dizziness.

### Sample size

Based on our clinical experience, changes in the NDLQI scores in the compatible acupoint group, single acupoint group and sham acupuncture group at the 4th week are expected to be 12, 8, and 4, respectively. The standard deviations in the three groups are expected to be 10, 13, and 13, respectively. The two-sided significance level is 0.05.
$$ n=\frac{\psi^2\left(\sum {S}_i^2/k\right)}{\sum {\left({\overline{X}}_i-\overline{X}\right)}^2/\left(k-1\right)} $$

A sample size of 60 patients in each group is estimated to have 80% power to detect significant differences among the three groups. To compensate for a 20% loss to follow-up, the sample size was increased to 72 patients.

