## Method/design

### Study design

This is a parallel randomized controlled study conducted in the First Affiliated Hospital of Changchun University of Chinese Medicine in China. Two hundred and sixteen FD patients will be recruited and randomized into one of three groups in a 1:1:1 ratio of the compatible acupoints group, single acupoint group, and sham acupuncture group. The three phases include a 1-week baseline period, a 4-week treatment period, and a 4-week follow-up period. Figure 1 shows the flow diagram of the trial. The study will be conducted in accordance with the Declaration of Helsinki and has been approved by the Ethics Committee of the First Affiliated Hospital of Changchun University of Chinese Medicine (CCZYFYLL2018–011-1). We have registered in the Acupuncture-Moxibustion Clinical Trial Registry (AMCTR-IPC-18000176) and Chinese Clinical Trial Registry (ChiCTR1900023983). Written informed consent will be obtained from each participant before randomization. The Standard Protocol Items: Recommendations for Interventional Trials (SPIRIT) 2013 checklist [13] is provided in Additional file 1.

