### Statistical analysis

The intention-to-treat analysis will be used for all allocated participants in the baseline condition. Baseline characteristics will be summarized across the treatment groups. Missing values will be imputed by the last observation carried forward (LOCF) method. Depending on whether the data are normally distributed, the continuous variables will be described as the mean (standard deviation) or the median (interquartile range). One-way analysis of variance (ANOVA) will be used for comparisons among the three groups. Categorical variables will be described using frequency (percentage) and compared using Fisher’s exact test. The statistical analyses will be performed using SAS 9.1.3. *P* < 0.05 will be considered statistically significant.

All efficacy analyses, which will include all participants who are randomized, will be performed using the intent-to-treat analysis. Primary comparisons (change in the NDLQI scores at week 4 relative to the baseline scores among the three groups) will be made with ANOVA. Pairwise comparisons will use the Student-Newman-Keuls method.

For the secondary outcomes, continuous variables, including the DSSS and SF-36 scores, metabolomics, and UPE, will be compared among the three groups at all follow-up time points using ANOVA. The Student-Newman-Keuls method will be used for pairwise comparisons. The OTE and adverse events will be summarized for each group and compared using Fisher’s exact tests.

Analysis of covariance (ANCOVA) or logistic regression analysis will be used in the sensitivity analysis. The sensitivity analysis will also be performed using a per-protocol analysis, which includes only those who complete ≥16 sessions and have no major protocol violations (e.g., taking other drugs during the trial).

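### The stated 80% power at 60 per group does not follow from the plan's own formula and inputs: 80% needs about 45 per group, and 60 gives about 91%

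*Protocol article*

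**What the plan says.** The Sample size section of the protocol article bases the calculation on clinical experience. The mean changes in the Nepean Dyspepsia Life Quality Index (NDLQI) for the compatible, single and sham groups "at the 4th week are expected to be 12, 8, and 4, respectively". On variability it says: "The standard deviations in the three groups are expected to be 10, 13, and 13, respectively". On the error rate: "The two-sided significance level is 0.05". It then prints the usual k-group formula, in which n equals psi squared times the mean within-group variance, divided by the between-group variance of the means. The value of psi is not given. The conclusion, for the comparison across all three arms, is: "A sample size of 60 patients in each group is estimated to have 80% power". An allowance for attrition follows: "To compensate for a 20% loss to follow-up, the sample size was increased to 72 patients".

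Two other places fix the test being powered. Under Study design, patients are "randomized into one of three groups in a 1:1:1 ratio". Under Statistical analysis: "Primary comparisons (change in the NDLQI scores at week 4 relative to the baseline scores among the three groups) will be made with ANOVA". Neither section splits the 0.05 level across comparisons.

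**The concern.** The section gives means, standard deviations, alpha, formula, sample size and power. Psi is determined by alpha, the number of groups and the power, so nothing is left free and the parts should agree. They do not. With the printed inputs the formula gives a sample size well below 60 for 80% power, and 60 is close to what 90% power would require.

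What is at stake is whether the recruitment target is justified as stated. If the target of 80% and the inputs are both right, the formula supports about 45 per group before attrition, not 60. If one of the inputs is misprinted, for example because the standard deviations used were larger, the real margin is unknown. A reader cannot tell which applies.

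**Working it through.** **Inputs** (Sample size section unless noted)

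- Means 12, 8, 4; grand mean 8.
- Standard deviations 10, 13, 13.
- Alpha 0.05; k = 3 equal groups (allocation from Study design).
- Test: one-way ANOVA on the week-4 change (Statistical analysis).
- Claimed result: 60 per group, 80% power.

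**Step 1: the plan's formula**

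- Mean within-group variance: (10² + 13² + 13²)/3 = (100 + 169 + 169)/3 = 438/3 = 146.
- Between-group variance: [(12−8)² + (8−8)² + (4−8)²]/(3−1) = (16 + 0 + 16)/2 = 16.
- n = psi² × 146/16 = 9.125 × psi².

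**Step 2: psi for the stated alpha**

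With numerator degrees of freedom 2 and infinite denominator degrees of freedom, psi = √(lambda/2). Here lambda is the noncentrality at which a chi-square test on 2 degrees of freedom at 0.05 has the required power.

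| Power | psi | n = 9.125 × psi² |
|---|---|---|
| 80% | 2.195 | 44.0 |
| 90% | 2.515 | 57.7 |

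Working backwards, n = 60 corresponds to psi = √(60/9.125) = 2.56. That lies slightly above the 90% value and well above the 80% value.

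**Step 3: exact check**

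Noncentral F with degrees of freedom 2 and 3(n−1), and lambda = 32n/146:

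| n per group | Power |
|---|---|
| 44 | 79.1% |
| 45 | 80.0% |
| 59 | 90.1% |
| 60 | 90.6% |

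The smallest n is 45 for 80% and 59 for 90%. The plan's pair of 60 and 80% is not reproduced. The approximate and exact answers differ by only one or two patients, so rounding does not explain the gap. A simulation that keeps the unequal standard deviations 10, 13 and 13 gives 81.3% at 45 and 91.8% at 60, so pooling the variances does not explain it either.

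**Step 4: after attrition**

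A 20% loss from 72 leaves 72 × 0.8 = 57.6 per group. The F-test power is 89.0% at 57 and 89.6% at 58, so it stays at about 89%.

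**Step 5: other routes to 60**

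| Variant | n for 80% power | Power at 60 |
|---|---|---|
| SD 13 in all groups | 52 | 85.8% |
| SD 14 in all groups | 61 | 80.0% |
| F test at alpha 0.05/3 | 59 | 81.1% |
| Two-group test, compatible vs sham, alpha 0.05 | 33 | 96.5% |
| Two-group test, compatible vs single, alpha 0.05 | 132 | 47.2% |
| Two-group test, single vs sham, alpha 0.05 | 166 | 39.2% |

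Only a common standard deviation of 14 or an alpha of 0.05/3 comes close to 60 at 80% power, and both contradict the printed inputs.

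**The case against.** The arithmetic is not in dispute. The strongest objection concerns cause and consequence.

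On cause, psi is not printed, so nobody can show that 60 is a 90% answer carrying the wrong label. The 90% answer is 58 or 59, not 60. An F test at 0.05/3 fits about as well. Small shifts in the means would also do it: 11.5, 8 and 4.5 with the printed standard deviations give 81.1% at 60. This point stands. The mismatch is established; its source is not. But these routes all need inputs that the section does not state, so they do not rescue the sentence as written.

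On consequence, the error is conservative. The planned number exceeds what the stated target needs, power remains about 89% after the anticipated loss, and no analysis or type I error rate changes. This also stands, and it limits the seriousness of the point. It does not make the stated power correct. Nor does it reassure if an input, rather than the power, is the misprint.

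The objection also holds that the power for compatible versus single acupoint is a separate question. That is fair: the discrepancy does not depend on it. It matters here only because a corrected figure of about 90% for the overall test should not be read as power for that comparison.

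**Conclusion.** The statement is wrong as written. Under means 12, 8 and 4, standard deviations 10, 13 and 13, and alpha 0.05, 60 per group gives 90.6% power for the three-group ANOVA, and 80% power needs 45 per group. The discrepancy is 60 − 45 = 15 patients per group, or 90.6 − 80 = 10.6 points of power. The result assumes normal data, a single F test at 0.05 and 60 analysed patients per group; unequal variances do not alter it materially. Whether the power or one of the inputs is the misreported item cannot be settled from the article.

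**What to change.** 1. Confirm the psi, alpha, means and standard deviations used in the calculation, and print psi.
2. If the printed inputs are right, restate the conclusion: 60 per group gives about 90% power (90.6%) for the three-group ANOVA, and 45 per group would give 80%.
3. If 80% was intended under other inputs, such as larger standard deviations or a divided alpha, replace the printed inputs with those.
4. Say that the figure refers to the overall F test, and report the compatible-versus-single power separately. Under the printed inputs that 4-point difference has about 47% power at 60 per group in an unadjusted two-group test, and about 43% by simulation under the planned Student-Newman-Keuls procedure.

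The cost is the rewording of one paragraph. Enrolment and the analysis are unchanged.

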### Statistical analysis

The intention-to-treat analysis will be used for all allocated participants in the baseline condition. Baseline characteristics will be summarized across the treatment groups. Missing values will be imputed by the last observation carried forward (LOCF) method. Depending on whether the data are normally distributed, the continuous variables will be described as the mean (standard deviation) or the median (interquartile range). One-way analysis of variance (ANOVA) will be used for comparisons among the three groups. Categorical variables will be described using frequency (percentage) and compared using Fisher’s exact test. The statistical analyses will be performed using SAS 9.1.3. *P* < 0.05 will be considered statistically significant.

All efficacy analyses, which will include all participants who are randomized, will be performed using the intent-to-treat analysis. Primary comparisons (change in the NDLQI scores at week 4 relative to the baseline scores among the three groups) will be made with ANOVA. Pairwise comparisons will use the Student-Newman-Keuls method.

For the secondary outcomes, continuous variables, including the DSSS and SF-36 scores, metabolomics, and UPE, will be compared among the three groups at all follow-up time points using ANOVA. The Student-Newman-Keuls method will be used for pairwise comparisons. The OTE and adverse events will be summarized for each group and compared using Fisher’s exact tests.

Analysis of covariance (ANCOVA) or logistic regression analysis will be used in the sensitivity analysis. The sensitivity analysis will also be performed using a per-protocol analysis, which includes only those who complete ≥16 sessions and have no major protocol violations (e.g., taking other drugs during the trial).

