### Outcomes

The following outcomes will be assessed by independent outcome assessors. These assessors will be trained before participating in this trial and will be blinded to the group assignments. The outcome assessors will contact the participants on the phone up to three times if the participants do not respond to the assessment. The outcome assessments will be performed at three time points: at baseline, at the end of the acupuncture treatments, and at the end of the follow-up period (Fig. 3). Patient privacy information will be separated from the trial data, and the analysis and publication of trial data results will not involve patient privacy information.

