#### Primary outcome

The primary evaluation index in the trial will be the change in scores on the Nepean Dyspepsia Life Quality Index (NDLQI) from baseline through the 4-week follow-up period. The NDLQI [19] is a disease-specific scale of quality of life that includes four aspects: life interference (13 items), knowledge/control (seven items), drinking/eating (three items), and sleep/disturbance (two items). Each item contains five options, corresponding to 1 to 5 points. The sum score = 100-[(actual raw score − lowest possible raw score)/raw score range] × 100. Higher scores indicate a better quality of life.

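### With no assessment between baseline and week 4, LOCF scores every participant who lacks a week-4 NDLQI as exactly zero change

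*Protocol article*

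**What the plan says.** All references are to the protocol article.

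- **Missing data** (Statistical analysis): "Missing values will be imputed by the last observation carried forward (LOCF) method".
- **Population** (same section): "All efficacy analyses, which will include all participants who are randomized, will be performed using the intent-to-treat analysis".
- **Primary test** (same section): "Primary comparisons (change in the NDLQI scores at week 4 relative to the baseline scores among the three groups) will be made with ANOVA". For comparing two groups at a time, Student-Newman-Keuls is named.
- **Schedule** (Outcomes): assessments are "performed at three time points: at baseline, at the end of the acupuncture treatments, and at the end of the follow-up period". The section on laboratory tests limits UPE and metabolomics to baseline and end of treatment.
- **Expected loss** (Sample size): "To compensate for a 20% loss to follow-up", the group size goes from 60 to 72. Neither the timing of the loss nor a rate by arm is given.
- **Sensitivity analyses** (Statistical analysis): ANCOVA or logistic regression, and a per-protocol analysis of those with at least 16 sessions and no major violation.

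**The concern.** LOCF needs an earlier value to carry. Before week 4 the only one is baseline, so for the primary comparison the rule amounts to carrying the baseline forward: the change is zero and no uncertainty is attached to it. For UPE and metabolomics it can never be anything else. For a participant lost after week 4, the end-of-treatment score is carried to the end of follow-up, which assumes no relapse.

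A zero change conflicts with the plan's own expectation that all three arms improve, sham included, and it departs most from expectation in the arm expected to do best. At stake is the estimate for the trial's main question, compatible acupoints (A) against single acupoint (B), where the expected gap is only 4 points. If loss differs by arm, the rule itself produces or hides a difference.

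**Working it through.** **Inputs from the Sample size section.** Mean changes at week 4 are 12, 8 and 4 in A, B and C (sham); SDs are 10, 13 and 13; alpha is 0.05 two-sided; there are 72 per group after a 20% allowance.

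**Assumed, because the document does not say.** The share p of each arm with no week-4 score, and that within an arm those missing would have changed by the same average as those observed.

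**The plan's own figure.** The plan gives no figure for the effect of LOCF. Its sample-size formula uses a mean variance of (100 + 169 + 169)/3 = 146 and a between-group term of (16 + 0 + 16)/2 = 16. Exact ANOVA needs 45 per group for 80% power and 59 for 90%, so the stated 60 fits 90%, not 80%. That is a separate matter and does not affect this point. With 72 complete cases per group, omnibus power is 95%.

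**Formulae under LOCF.**
- Analysed mean = (1 − p)μ
- Analysed variance = (1 − p)SD² + p(1 − p)μ²
- Analysed A−B = (1 − pA)μA − (1 − pB)μB

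**Equal loss.**
- p = 0.10 (about 7 of 72): means 10.8, 7.2 and 3.6; A−B = 3.6.
- p = 0.20 (about 14 of 72): means 9.6, 6.4 and 3.2; A−B = 3.2.
- Variances at p = 0.20: A 80 + 23.04 = 103.04 (SD 10.15); B 135.2 + 10.24 = 145.44 (SD 12.06); C 135.2 + 2.56 = 137.76 (SD 11.74). The SDs move little.

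Simulating the planned ANOVA with Student-Newman-Keuls at p = 0.20 gives:

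| | LOCF, 72 per group | Observed cases only |
|---|---|---|
| Omnibus power | about 87–88% | about 90–91% |
| A−B power | about 38% | about 41% |

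LOCF keeps all 216 participants in the analysis yet has slightly less power than the observed data alone. Type I error is not inflated: with A = B = 8 and C = 4, A−B is rejected in about 3.5% of trials.

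**Unequal loss, true A−B = 4.**
- 30% in A, 10% in B: 0.7 × 12 − 0.9 × 8 = 8.4 − 7.2 = 1.2.
- 10% in A, 30% in B: 0.9 × 12 − 0.7 × 8 = 10.8 − 5.6 = 5.2.

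**Unequal loss, no true A−B difference (both change 8; 20% loss in C).**
- 10% in A, 30% in B: 7.2 − 5.6 = a false difference of 1.6. The planned procedure rejects A−B in about 7% of trials if sham also changes 8, and in about 11% if sham changes 4.
- 15% in A, 25% in B: 6.8 − 6.0 = 0.8. With sham changing 4, rejection is about 5%.

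**The case against.** Several arguments limit the point, and most of them stand.

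- **Stopping treatment is not the same as missing the assessment.** A reader might infer that every early dropout is scored zero. The documents do not support that: LOCF acts on missing scores, and assessors telephone non-responders up to three times. Someone who stops needling but is still assessed keeps an observed value.
- **The 20% need not fall before week 4.** There is a further 4-week follow-up period, so 20% missing at week 4 is an upper case within the plan's allowance. This is why 10% is shown beside it.
- **The imbalance is assumed.** The plan gives one loss rate for all arms, intends participants to be blinded, and uses the same number of sessions and the same apparatus throughout. Arms do differ in needle number, site and de qi, so unequal loss is possible, but nothing in the text points to 10% versus 30%.
- **A simple two-arm z-test gives larger figures.** It yields about 15% false rejection at 10% versus 30% loss, and A−B power of 41% against 46% at equal 20% loss. Those are not error rates or power for the planned three-group procedure and should not be quoted as such.
- **The per-protocol analysis is a partial check.** It would remove most people who leave during treatment. However, it selects on adherence after randomisation and does not state a different missing-data assumption.
- **The alternative is also an assumption.** For someone with no score after baseline, a model under missing at random has only baseline and group to use, and supposes that such a person responds like similar completers. The gain is an explicit assumption and honest uncertainty, not certainty about the missing values.

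It might also be said that zero change is deliberately cautious. That does not stand: the bias runs in either direction, depending on which arm loses more people.

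**Conclusion.** The point holds in this form: every participant without a week-4 NDLQI is analysed as zero change, as if observed, against the plan's own expected improvements. This follows from the stated text and is not something left to another document.

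The Primary outcome section words the endpoint differently, as change "from baseline through the 4-week follow-up period". On that reading a participant lost after week 4 takes the week-4 score, but one with no score after baseline is still zero. The no-relapse assumption concerns only those lost after week 4; it would be too much to say that all follow-up results lean towards a maintained effect, since earlier losses stay at zero.

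Under equal loss the harm is modest: up to 20% attenuation and about three points of power. The serious risk is bias when loss differs by arm, and its size depends on rates the documents do not give. Serious inflation of type I error needs a large imbalance. This is a should-fix; a reader might infer that the rule invalidates the primary analysis, and the figures for the planned procedure do not support that.

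**What to change.** In the Statistical analysis section, replace LOCF for the primary and continuous secondary outcomes with one of these:

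- a likelihood-based repeated-measures model with group, visit, group-by-visit and baseline; or
- multiple imputation under missing at random, using baseline, group and the other visit.

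Keep LOCF only as a sensitivity analysis, and add one simple missing-not-at-random analysis, for example delta-adjusted. Report the number without a week-4 score in each arm. Settle the choice before allocation is revealed, since a missing-data method chosen afterwards would be open to challenge.

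The cost is a change of wording and slightly more analysis work, with no new visits or data. The downside is that missing at random is itself untestable, which is why the additional sensitivity analysis is needed.

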#### Secondary outcomes

##### Dyspeptic symptom sum score (DSSS)

The mean change of dyspeptic symptom sum score (DSSS) [20] from baseline is used to evaluate the severity level of four main symptoms: postprandial fullness, early satiety, epigastric pain, and epigastric burning sensation. Each symptom will be scored as follows: 0 (none), 2 (mild: spontaneous remission within 1 h after meal), 4 (moderate: ease within 1–3 h after meal), and 6 (severe: relief after > 3 h and/or treatment needed). All scores are added up to obtain a sum score between 0 and 24. Higher scores indicate more severe symptoms.

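### The response variable in the ANOVAs of DSSS, SF-36 and UPE does not match their definition as change from baseline; fix it as change, adjusted for baseline

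*Protocol article*

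**What the plan says.** In the protocol article, the three outcomes are introduced in terms of change:

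- DSSS: "The mean change of dyspeptic symptom sum score (DSSS) [20] from baseline is used to evaluate the severity level of four main symptoms".
- SF-36: "The health state will be evaluated by the mean change of SF-36 [22] from baseline".
- UPE, under Laboratory tests: "The purpose of this test is to detect mean changes in UPE before and after acupuncture".

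The Statistical analysis section then states how the continuous secondary variables are tested: they, "including the DSSS and SF-36 scores, metabolomics, and UPE, will be compared among the three groups at all follow-up time points using ANOVA". Pairwise comparisons follow by the Student-Newman-Keuls method. ANCOVA appears only as a sensitivity analysis, with no covariate or response named.

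The paragraph before it in the same section is explicit about the primary outcome: "Primary comparisons (change in the NDLQI scores at week 4 relative to the baseline scores among the three groups) will be made with ANOVA".

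Under Outcomes, clinical assessments fall at baseline, end of treatment and end of follow-up. For UPE, Laboratory tests says: "These measurements will be performed at the baseline and at the end of the treatment time points". Metabolomics has the same two times.

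**The concern.** Whoever programs the secondary ANOVAs must decide what goes on the left-hand side of the model. The outcome definitions point to change from baseline. The analysis sentence, read on its own, points to the score observed at each time. The explicit wording for NDLQI, one paragraph earlier, makes the silence about change harder to pass over.

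The choice has consequences. A chance imbalance at baseline enters the two comparisons in opposite directions, and their precision differs by an amount that depends on a correlation the document does not give. The same data can therefore give a significant result on one variable and not on the other. If the choice is still open when the data are analysed, it could be influenced by the results.

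**Working it through.** **Text.** Each outcome has one definition and one analysis statement.

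| Outcome | Definition | Analysis statement | Post-baseline times |
|---|---|---|---|
| NDLQI (primary) | change | change, at week 4 | two |
| DSSS | mean change | scores, at follow-up times | two |
| SF-36 | mean change | scores, at follow-up times | two |
| UPE | mean change (aim of test) | UPE, at follow-up times | one |

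The wording differs between the two sections for the last three rows. Nothing else in the article says which variable enters the ANOVA. There is no stated figure to reproduce.

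**Inputs for the size.** From the document: three equal arms, 60 per arm before the allowance for loss and 72 randomized per arm, significance at 0.05. Assumed, because the document does not give them: the same SD at baseline and follow-up (set to 1), bivariate normal data, and a baseline to follow-up correlation r of 0.3, 0.5 or 0.7.

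**Expected difference.** Randomization makes the expected baseline means equal, so the expected group difference in change equals that in score. In a given trial, a baseline difference d shifts the score difference by r × d on average and the change difference by r × d − d = −(1 − r) × d. The signs are opposite.

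**Precision.** Per-patient variance of each response:

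- score: 1
- change: 1 + 1 − 2r = 2(1 − r)
- baseline-adjusted: 1 − r²

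| r | Score | Change | Adjusted |
|---|---|---|---|
| 0.3 | 1 | 2 × 0.7 = 1.40 | 1 − 0.09 = 0.91 |
| 0.5 | 1 | 2 × 0.5 = 1.00 | 1 − 0.25 = 0.75 |
| 0.7 | 1 | 2 × 0.3 = 0.60 | 1 − 0.49 = 0.51 |

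The adjusted variance is never larger than the others: 1 − r² ≤ 1, and 1 − r² = (1 − r)(1 + r) ≤ 2(1 − r). In a finite sample, adjustment also costs one degree of freedom and a small penalty for chance imbalance.

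**Agreement of the two estimates.** Their correlation is (1 − r)/√(2(1 − r)), which is 0.59, 0.50 and 0.39 for the three values of r.

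**Simulation.** One-way ANOVA of score and of change on the same patients, 60 per arm, 10,000 trials per setting. The effect setting has group means of 0.5, 0.25 and 0 SD.

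| r | Power, score | Power, change | Verdicts differ | No effect: at least one significant |
|---|---|---|---|---|
| 0.3 | 69% | 53% | 33% | 9.0% |
| 0.5 | 68% | 68% | 31% | 8.7% |
| 0.7 | 67% | 90% | 31% | 9.4% |

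With no effect, each test alone rejects in 4.6% to 5.1% of trials.

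With 72 per arm and an effect that gives the score ANOVA 80% power, the change ANOVA has 65%, 80% and 96% power, and the verdicts differ in about 28%, 23% and 20% of trials. The rate of at least one significant result with no effect is again about 9%. The disagreement rate therefore depends on the assumed effect and sample size; the 9% hardly does.

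**Why adjustment removes the question.** If score = a + τ(group) + βX + error, with X the baseline value, then change = score − X = a + τ(group) + (β − 1)X + error. Only the coefficient of X differs. The group effect, its standard error and its p-value are identical.

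**The case against.** The best defence is that the sections can be read together. The analysis sentence is introduced as applying to the secondary outcomes, which have already been defined in terms of change. On that reading, DSSS and SF-36 scores simply names the instruments, and the sentence adds only the test and the times. It nowhere says raw or absolute values. This stands: a reader might infer that the plan definitely analyses something other than its defined outcomes, but the text does not go that far. What remains is that the reader has to supply the word, in a section that supplies it for NDLQI.

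A reader might also see a second contradiction, because UPE and metabolomics have only one post-baseline measurement while the sentence refers to all follow-up times. The sentence covers four kinds of variable at once, and the phrase naturally means the times scheduled for each. No second laboratory measurement is promised, so this needs clarifying wording and nothing more.

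Nor are there two estimands. Since the expected group difference is the same, the issue is the estimator and its precision.

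It can be added that the response variable of a secondary ANOVA is a detail often left to an analysis plan, which is not shown. That would answer an omission. Here the article makes statements in two places and they do not match.

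Finally, replacing ANOVA by a covariate model goes further than inserting a missing word. That is true and should be acknowledged as a change of method. It is justified because adjustment makes the score-or-change question irrelevant and is at least as precise as either ANOVA, apart from the small finite-sample cost.

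**Conclusion.** The point holds as an inconsistency that should be corrected, of moderate weight. As written, the response variable of the DSSS, SF-36 and UPE ANOVAs does not match the outcome definitions, and the stated main analysis makes no use of the baseline value as a covariate.

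Over r from 0.3 to 0.7, the change score ranges from less precise than the follow-up score (variance ratio 1.40) to clearly more precise (0.60). The two ANOVAs gave different significance verdicts in roughly 20% to 33% of simulated trials with a real effect. These figures rest on equal SDs, normality and assumed effects, none of which the document gives.

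The 9% should not be read as the error rate of the plan. It arises only if an analyst runs both tests and reports the better one, which nothing in the article proposes. With either variable fixed in advance, the rate stays near 5%. The primary NDLQI comparison is not affected by this point.

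**What to change.** In the Statistical analysis section, state that the secondary analysis is of change from baseline in DSSS, each SF-36 subscale and UPE, compared among the groups by ANCOVA with that outcome's own baseline value as covariate. Give the times for each outcome: end of treatment for all, and end of follow-up for DSSS and SF-36 only. Say in the same place that metabolomics has end of treatment as its only post-baseline time. State that pairwise comparisons are made on the baseline-adjusted means.

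If the sponsor prefers to keep ANOVA as the main secondary analysis, the minimum is to name change from baseline as its response, in the same words as the outcome definitions.

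The cost is a few sentences and a change of role for ANCOVA, which the section already lists as a sensitivity analysis. The baseline values are already collected, and no further patients or visits are needed. The change should be fixed before the allocation is revealed.
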